**3.1.4 Suspension criteria**

- Should a participant express a desire to discontinue their involvement in the study at any point, their request will be honored, and they will be withdrawn from the clinical trial.
- Participants who are untraceable or fail to attend scheduled follow-up assessments will be considered lost to follow-up and subsequently withdrawn from the study.
- In the event that a participant develops new comorbidities, complications, or undergoes physiological changes during the study that render them unsuitable for continued intervention, they will be removed from the trial.
- If a participant’s health status significantly worsens during the study, potentially leading to a critical event, and the supervising physician deems it necessary to halt the clinical trial for the individual’s safety, the participant will be withdrawn from the study.

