**3.1.5 Elimination criteria**

- Participants who are subsequently found to not fulfill the inclusion criteria after the commencement of the study will be excluded.
- Subjects who decline to participate in the prescribed examination and assessment protocol during the study will be withdrawn.
- Participants demonstrating suboptimal adherence, with cumulative exercise time falling below 80% of the prescribed amount, or those who consume medication that influences muscle or bone metabolism during the study period, will be considered non-compliant and thus removed from the trial.

1. **Sample size**

The prevalence of functional falls and fractures is a significant clinical concern and a severe consequence for patients with sarcopenia, stemming from the progressive loss of muscle mass and function. The Simple Physical Performance Measurement Scale (SPPB) serves as a pivotal efficacy indicator in this context. Drawing from extant literature ^[14]^, a 24-week exercise intervention in elderly patients with a heightened risk of falls yielded an SPPB score of 9.83 ± 1.85 in the experimental group, compared to 8.39 ± 2.52 in the control group. Employing a two-sided test with an alpha level (α) of 0.05 and a power (test efficacy) of 0.9, the calculated sample size for a single group is n = 35.6, which approximates to 36 participants. Consequently, the combined sample size for both groups amounts to 72 individuals. Factoring in a dropout rate of 20%, the total sample size required for this study is 90 cases, equating to 45 participants per group.

1. **Participant**

The proposed study aims to enroll 90 elderly patients with sarcopenia who visited the Hospital of Chengdu University of Traditional Chinese Medicine between July 2022 to August 2023. The process for inclusion involves a meticulous screening of candidates at the outpatient clinic. Potential participants are to be thoroughly informed about the study’s objectives, procedures, and potential risks. Following this educational dialogue, those who meet the study criteria and express a willingness to participate will be asked to provide informed consent and sign the corresponding consent form.

1. **Randomization and Blinding**

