The random allocation sequence was delegated to a specialized statistical analyst, who utilized the SAS 9.4 software (SAS, USA) to generate a series of random numbers ranging from 1 to 90. Subsequently, the analyst enumerated the eligible participants in sequential order of their enrollment and allocated them randomly in a balanced 1:1 ratio to either the Baduanjin exercise intervention cohort—hereinafter referred to as the ‘Baduanjin group’—or the resistance training comparator arm—hereafter denoted as the ‘control group’. The integrity of the randomization sequence was preserved by the study administrator, who remained uninvolved in participant recruitment, outcome evaluation, and statistical analysis. Upon completion of all initial assessments, participants were apprised of their group assignment via telephone.

Due to the nature of the intervention, it was impracticable to blind the study participants. Consequently, blinding was confined to the outcome assessment, data management, and statistical analysis phases. In lieu of explicit group identifiers, the designations ‘A’ and ‘B’ were employed on the case report forms to maintain anonymity. An independent statistical expert, external to the participant cohort, employed SAS software to create the blind base—a table of random numbers—which was subsequently safeguarded by the study administrator. The statistician tasked with data analysis remained uninformed about the specific intervention programs administered to each group. This blinding was only disclosed subsequent to the completion of all statistical analyses.

1. **Interventions**

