**8.3 Secondary outcomes**

The methodology for assessing the efficacy of the intervention on elderly patients with sarcopenia is comprehensive and multi-faceted, involving the following measures:

- Body Composition Analysis: Utilizing the DBA-510 Body Composition Analyzer, participants' body weight, body water, fat mass, fat percentage, lean body weight, BMI, and segmental muscle mass of the trunk, upper, and lower limbs will be evaluated through bioelectrical impedance analysis.
- Handgrip Strength Measurement: The JAMAR electronic grip strength meter will be employed to gauge upper limb muscle strength. Participants will perform the test standing, with arms at their sides, elbows bent at 90°, and forearms supinated, exerting maximum grip strength. The highest value from four measurements (two per side) will be recorded.
- 6-Meter Walk Test: This test assesses muscle performance by having participants walk 6 meters at their usual pace. The walking speed is calculated based on the time taken to complete the distance. The test is conducted twice, and the average time and speed are noted.
- Cognitive Function Assessment: The 30-item Montreal Cognitive Assessment (MoCA, Changsha version) will be used to measure global cognitive function. This instrument is tailored for Chinese populations and scores cognitive function across multiple domains on a scale from 0 to 30, with higher scores indicating better cognitive function.
- Incidence of Falls Tracking: Participants will maintain a "fall calendar" diary to document any falls and related medical consultations monthly. This includes accidental landings on the floor or ground or collisions with objects. The collection of fall data commences with the first intervention class and continues until the intervention's conclusion or until a participant's withdrawal, death, or loss to follow-up.

1. **Quality control**

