**Table 2. Schedule of trial procedures**

| **Period** | **Screening** | **Intervention period** | | |
| --- | --- | --- | --- | --- |
| **Time point** | **0 wk** | **0 wk** | **12 wk** | **24 wk** |
| **Enrollment** | **×** |  |  |  |
| Eligibility screening | **×** |  |  |  |
| Informed consent |  | **×** |  |  |
| **Allocation** |  |  |  |  |
| **Intervention** |  |  |  |  |
| Non-sarcopenia control |  | **×** |  |  |
| Baduanjin exercise |  | **×** | **×** | **×** |
| Resistance training |  | **×** | **×** | **×** |
| **Assessments** |  |  |  |  |
| Physical function |  | **×** | **×** | **×** |
| Body composition |  | **×** | **×** | **×** |
| Handgrip strength |  | **×** | **×** | **×** |
| 6 m walking test |  | **×** | **×** | **×** |
| Cognitive function |  | **×** | **×** | **×** |
| Incidence of falls |  | **×** |  | **×** |

1. **References**
2. Morley JE. Sarcopenia:diagnosis and treatment[J]. *J Nutr Health Aging,* 2008, 12: 452-456.
5. Cao Li MD, JE. Morley MB. Sacropenia is recognized as an independent Condition by an International Classification of Disease, Tenth Revision, Clinical Modification(ICD-10) Code[J]. 2016, (17): 675-677.
6. Murton AJ. Muscle protein turnover in the elderly and its potential contribution to the development of sarcopenia[J]. *Proc Nutr Soc*, 2015:74(4): 387-396.
7. Yuwei Lin, Guiyu Qian, Meizhi Xu. Causes and effects of sarcopenia in the elderly[J].*Tertiary sports*, 2010.10, (110): 85-91.

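### Fall recording runs from the first class to withdrawal, so randomised people who never start have no defined fall follow-up and early leavers are censored; Table 2 does not match the monthly diary

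*Combined protocol and SAP*

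**What the plan says.** Falls are a secondary outcome in 8.3, kept by the participant in a monthly diary. The start is fixed by the statement that "The collection of fall data commences with the first intervention class". The end is fixed in the same sentence: collection "continues until the intervention's conclusion or until a participant's withdrawal, death, or loss to follow-up".

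Section 6 places allocation before any class: "Upon completion of all initial assessments, participants were apprised of their group assignment via telephone". Participants are not blinded.

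Two other rules can end a participant's time in the trial. Under 3.1.4, people who cannot be traced or who miss follow-up assessments "will be considered lost to follow-up and subsequently withdrawn from the study", and people with new complications or worsening health are also withdrawn. Under 3.1.5, people whose cumulative exercise time is below 80% of the prescribed amount "will be considered non-compliant and thus removed from the trial".

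In Table 2 the row "Incidence of falls" is marked at weeks 0 and 24. The other five assessment rows are marked at weeks 0, 12 and 24. Section 10.2 names intention-to-treat as the approach and GEE as the model. It does not say how falls will be summarised when follow-up differs between people.

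**The concern.** In a randomised comparison the clock for an event outcome should start at randomisation and run for everyone randomised. Here both ends of the fall record depend on what happens after allocation.

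- **Start.** A person can hear the assigned arm by telephone and decide not to attend. The arms are different kinds of exercise and participants know which they have, so the decision not to start may differ by arm.
- **End.** Recording stops at withdrawal, and several routes to withdrawal are plausibly linked to falling: a new complication, worsening health, or missed sessions after an injury. Censoring of that kind can understate the fall rate. It biases the comparison if the arms differ in how often, or why, people leave.

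The schedule adds a practical doubt. A monthly diary suggests regular retrieval, but the only post-baseline falls mark is at week 24, a visit that early leavers do not reach.

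Falls matter to this trial beyond being one item in a list. Sections 4 and 10.1 open with falls and fractures as the clinical consequence that motivates it.

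**Working it through.** The documents give no fall rate, event count or power for falls, so there is no stated figure to reproduce. The check has two parts: the text side by side, then the person-time exposed.

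**Text**

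1. *Order of events.* Baseline assessment, then the telephone call about allocation (section 6), then the first class, then the start of fall recording (8.3). The interval from allocation to first class is uncovered for everyone. For someone who never attends, no start is defined.
2. *End of recording.* 8.3 keeps early leavers in the record up to exit. What is lost is falls after exit.
3. *Adherence rule.* The prescribed amount is 24 weeks × 3 sessions = 72 sessions of 60 minutes. The 20% margin is 0.20 × 72 = 14.4 sessions, or 14.4 / 3 = 4.8 weeks of classes. An injury that keeps someone away for five weeks is enough to fall below 80%. If removal under 3.1.5 counts as withdrawal under 8.3, it ends that person's fall record. The documents do not say whether the rule is applied during the trial or only at the end.
4. *Retrieval.* Section 7.3 gives a telephone route for the daily-activity sheets. Nothing equivalent is given for the fall diary.

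**Person-time**

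Inputs: 90 randomised and "Factoring in a dropout rate of 20" per cent (section 4); 24 weeks of intervention (7.1, 7.2). Exit times and the number of never-starters are assumptions.

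- Full follow-up: 90 × 24 = 2,160 person-weeks.
- Dropouts: 0.20 × 90 = 18. Completers: 72 × 24 = 1,728 person-weeks (80%).
- Observed total = 1,728 + (dropouts who start) × (mean weeks before exit).

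| Assumption for the 18 | Observed person-weeks | Unobserved |
| --- | --- | --- |
| All start, mean exit week 18 | 1,728 + 18 × 18 = 2,052 | 108 (5%) |
| All start, mean exit week 12 | 1,728 + 18 × 12 = 1,944 | 216 (10%) |
| All start, mean exit week 6 | 1,728 + 18 × 6 = 1,836 | 324 (15%) |
| 3 never start, others week 12 | 1,728 + 15 × 12 = 1,908 | 252 (12%) |
| 6 never start, others week 12 | 1,728 + 12 × 12 = 1,872 | 288 (13%) |
| 9 never start, others week 12 | 1,728 + 9 × 12 = 1,836 | 324 (15%) |

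If none of the 18 ever started, 432 person-weeks (20%) would be unobserved, which is the ceiling at the planned dropout. In the first three rows the leavers also hold 324, 216 or 108 person-weeks of completed diary. 8.3 counts that time; only its retrieval is unspecified.

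**The case against.** The strongest reply is that 8.3 does include early leavers. A reader who looks only at the start rule and Table 2 might infer that people who leave early contribute no fall data. The sentence in 8.3 rules that out, because collection runs to withdrawal, death or loss to follow-up. Their completed diary pages would be lost only if diaries were collected solely at week 24. The documents do not say that, and section 9.3 has researchers on site at every session. This objection stands: the supportable statement is that retrieval is unspecified.

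Four further points have some weight.

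- *The first class might mean the scheduled start of the programme, not the first class a person attends.* The text allows this. Even so, the time from allocation to that date is uncovered, and anyone who withdraws before it has no record.
- *The week-0 mark may be legitimate.* Section 8.1 collects falls in the past year, and the mark could instead denote issue of the diary. It should be defined, not treated as an error.
- *Section 10.2 says that GEE accommodates incomplete data.* Standard GEE does not correct for dropout related to the outcome, and no follow-up-time term is specified for falls.
- *Bias between arms needs differential loss, and none is shown.* That is true of any plan before data exist. It limits the weight of the point but does not remove the conflict with intention-to-treat.

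**Conclusion.** The point holds as a gap in how falls are ascertained. Randomised people who never start have no defined fall follow-up. Those who leave early are censored at exit, possibly informatively. The monthly diary and Table 2 have not been reconciled. The first two do not fit the intention-to-treat approach in 10.2.

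At the planned 20% dropout, about 5% to 15% of planned person-time is unobserved under the assumed patterns, with a ceiling of 20%. These figures assume that the 20% covers all routes out of the trial. They measure follow-up time, not falls. A reader might want to convert them into a number of missed falls, but the documents give neither a fall rate nor a split of reasons for leaving, so no such number can be supported.

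The primary outcome, SPPB, is not affected, and falls have no sample-size basis of their own. This is a cheap improvement to a secondary outcome that bears on the trial's stated rationale.

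**What to change.** - **8.3, start and end.** State that fall recording begins on the day of allocation for every randomised participant and continues to week 24 regardless of class attendance or adherence, unless the participant withdraws consent for follow-up. State in 3.1.4 and 3.1.5 that leaving the intervention, or failing the adherence threshold, does not by itself end fall recording.
- **8.3, retrieval.** Retrieve diary pages monthly by the same route in both arms: at class, or by telephone for non-attenders. The four-weekly education session is not a safe vehicle, because its frequency is given only for the resistance arm (7.2) and not for Baduanjin (7.1).
- **Table 2.** Add a falls mark at week 12, and define the week-0 mark as baseline fall history or diary issue.
- **10.2.** Compare falls as a rate using each person's follow-up time, for example a count model with log follow-up time as an offset. Report by arm the number who never started, the person-time and the reasons for leaving.

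The cost is a few extra minutes per contact and some telephone calls to non-attenders; no new visit is needed. Anyone who refuses all further contact will still contribute little, so the change reduces the problem but does not abolish it.

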**7.2 The Resistance training Group**

The educational component of the study on sarcopenia in the elderly is structured to provide sessions once every four weeks, each lasting no less than 30 minutes. These sessions are designed to impart knowledge on the risk factors, adverse consequences, and preventive measures associated with sarcopenia. An example of such preventive measures includes adherence to the dietary guidelines for the elderly, as revised in 2016 by the Chinese Nutrition Society, which emphasizes rational nutrition, balanced diets, and the cultivation of healthy living and eating habits. In terms of physical intervention, the study incorporates a resistance training program tailored to the geographic location of each sub-centre. The regimen consists of 60-minute sessions conducted three times a week over a 24-week period. Each training session is segmented into a 15-minute warm-up, followed by 30 minutes of resistance exercises—including Wall squat, Wall push-up, Forward lunge, Reverse triceps push-up, and Wall-supported calf raise—and concludes with 15 minutes of cool-down activities.

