**8.1 Demographics**

For the comprehensive assessment of participants in your study on sarcopenia, the following data should be meticulously collected:

- Demographic Data: This includes the participant’s name, gender, date of birth, education level, weight, height (or BMI), ethnicity, occupation, and contact address.
- General Physical Examination: Vital signs such as heart rate, pulse, respiration, and blood pressure should be systematically recorded.
- Medical and Social History:
- Current Medical History: Document any present health conditions.
- Co-morbidities and Medications: List any concurrent illnesses and current medications.
- Allergies: Note any known allergies.
- Family History: Include any relevant hereditary health issues.
- Smoking and Alcohol History: Record past and present tobacco and alcohol use.
- Additional Relevant Information: Gather details on any falls within the past year, hand dexterity (sharp hands), sleeping habits, hobbies, personality traits, social activities, and other lifestyle factors that may influence the condition.

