**10.2 Data analyses**

Following an intention-to-treat (ITT) protocol, those whose cumulative time of exercise reaches 80% of the amount to be completed and not higher than 120% of that will be classified into per protocol set (PPS). Categorical variables will be presented as percentages or frequencies. As for continuous variables, normally distributed data will be described by mean ± standard deviation, while non-normally distributed data will be described using median [interquartile range (IQR)]. Baseline demographic descriptors and outcome measures wil be compared across groups by using analysis of variance for continuous variables and the $\chi$*^2^* (or Fisher exact) test for categorical variables. Within the scope of this investigation, the Generalized Estimating Equations (GEE) framework was employed to evaluate the impact of Baduanjin exercise on sarcopenia among the elderly cohort. GEE is a robust statistical approach designed to analyze correlated data or repeated measurements over time, rendering it particularly adept at accommodating incomplete datasets and multiple observational instances.Initially, an exhaustive data cleansing and encoding procedure will be undertaken to ascertain the precision and integrity of the dataset. Continuous variables will undergo a distributional analysis to discern the necessity of transformation to align with the normal distribution assumption. Categorical variables will be delineated through frequencies and percentages.The GEE model will incorporate temporal factors as a repeated measures variable, alongside other pertinent covariates that may influence the outcomes, such as age, gender, and baseline muscle mass index. The inclusion of interaction terms pertinent to time will facilitate an in-depth assessment of the longitudinal effects of Baduanjin exercise on sarcopenia. The model’s fit will be gauged using the Quasi-likelihood under the Independence model Criterion (QIC), with preference given to the model demonstrating the minimal QIC value. Additionally, a thorough examination of model residuals will be conducted to validate the adherence to underlying assumptions.Two-sided P values of less than 0.05 will be considered statistically significant. Analyses will be conducted using SPSS version 23.0 (IBM Corp) or GraphPad Prism version 7.0 (GraphPad Software).

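### Falls are recorded over follow-up of unequal length, but no method named in the plan takes account of time at risk

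*Combined protocol and SAP*

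**What the plan says.** Falls are a secondary outcome. Section 8.3 has participants keep a fall calendar, a "diary to document any falls and related medical consultations monthly". On the observation window it says: "The collection of fall data commences with the first intervention class and continues until" the intervention ends, or "until a participant's withdrawal, death, or loss to follow-up". Planned exposure is 24 weeks in both arms (7.1, 7.2). In Table 2 the row "Incidence of falls" is marked at week 0 and week 24 only, so falls have one scheduled entry after baseline.

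Early exits are expected. Section 4 states: "Factoring in a dropout rate of 20%, the total sample size required for this study is 90 cases". Section 3.1.4 withdraws participants for new illness or worsening health. Section 3.1.5 removes those who complete too little of the prescribed exercise, refuse assessments, or take medication that acts on muscle or bone.

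Section 10.2 invokes intention-to-treat. It says baseline descriptors and outcome measures will be "compared across groups by using analysis of variance for continuous variables", with chi-square or Fisher tests for categorical variables. It names GEE for evaluating the intervention, with time as a repeated-measures factor. It does not say whether falls are a count, a rate or a yes/no outcome, and it names no person-time denominator, count model or time-to-event model. Falls history is available at baseline, since 8.1 asks staff to "Gather details on any falls within the past year".

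**The concern.** A participant who leaves at week 8 has had a third of the planned 24 weeks in which to report a fall. Comparing raw totals, or proportions of fallers, treats that participant as if observed throughout. If the two programmes lose people at different rates, the difference in observation time passes into the comparison of falls. The arms do different exercises, and some exit rules depend on adherence or health, so equal loss cannot be taken for granted. Fall counts are also usually skewed, with many zeros and a few repeat fallers, which suits ANOVA poorly. What is at stake is the credibility of the falls comparison in a plan that itself treats falls as a serious consequence of sarcopenia (Sections 4 and 10.1).

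**Working it through.** **Inputs from the documents.** Follow-up is 24 weeks at most, there are 45 participants per arm, and overall dropout is 20%. The dropout step reproduces: 72 / (1 − 0.20) = 90. The plan gives no fall rate, dispersion, power for falls or dropout by arm, so there is no falls figure to reproduce.

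**Assumptions (not in the documents).** The true fall rate is the same in both arms. Loss is unrelated to falls. Leavers are observed for a mean fraction *f* of the 24 weeks (*f* = 0.5 if exits are uniform). All randomised participants stay in the denominator.

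**Formula.** With loss proportions d_H (higher) and d_L (lower), the expected ratio of mean falls, higher-loss arm to lower-loss arm, equals the ratio of person-time:

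[1 − d_H(1 − f)] / [1 − d_L(1 − f)]

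Every split below averages to the planned 20%.

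| Loss, lower / higher arm | f = 0.25 | f = 0.5 | f = 0.75 |
|---|---|---|---|
| 20% / 20% | 1.00 | 1.00 | 1.00 |
| 15% / 25% | 0.915 | 0.875/0.925 = 0.946 | 0.974 |
| 10% / 30% | 0.838 | 0.85/0.95 = 0.895 | 0.949 |
| 0% / 40% (extreme) | 0.70 | 0.80/1.00 = 0.80 | 0.90 |

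At 10%/30% and *f* = 0.5 the spurious reduction is 1 − 0.895 = 0.105, about 11%. Inverted, the ratio is 0.95/0.85 = 1.12.

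**Simulation.** This used 45 per arm, overdispersed counts (dispersion 1), equal true rates of 0.5 to 3 falls per person-year, and uniform exit times.

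- At 10%/30% the unadjusted ratio of mean falls was 0.88 to 0.89. Whole participants must leave, here 4 and 14 of 45, which gives (45 − 7)/(45 − 2) = 0.884.
- At 1 fall per person-year, the proportion of fallers was 30% versus 27% at 10%/30% loss, and 29% in both arms at 20%/20%.
- Dividing by person-time returned a rate ratio of 1.00, to within simulation error, in every setting.
- Type I error of a two-group ANOVA on counts was 4.4% to 4.9% at 20%/20%, 5.2% to 6.6% at 10%/30%, and 7% to 11% at 0%/40%.
- For the proportion of fallers at 10%/30% (1 or 2 falls per year), the uncorrected chi-square test gave 6.2% to 7.0%. Fisher's test, which the plan also names, gave 3.6% to 4.3%.

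**What the plan leaves open.** The result depends on how leavers are handled.

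1. If their truncated counts are kept, the bias above applies.
2. If they are set to missing at week 24, this bias goes, but falls already recorded are discarded, which sits badly with intention-to-treat.
3. If a GEE is fitted to monthly diary records, unobserved months drop out and exposure is partly allowed for.

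The plan does not say which applies, and Table 2 shows only one post-baseline entry.

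**The case against.** The strongest reply is that the plan is silent here rather than wrong. It does not exclude an offset; it states no family, link or offset at all. Nothing says falls will be averaged or dichotomised, and the outcome's name is compatible with a rate. The sentence naming ANOVA and chi-square can be read as covering baseline comparisons only. GEE is described as able to handle incomplete data, and a distributional check with possible transformation is planned. All of this is fair. But on the narrow reading falls are left with a model that is undefined for them, and a transformation does not supply a denominator.

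A reader might infer that the arm losing more people will look safer. The documents do not support that. They give one overall dropout figure and none by arm, and at equal loss the bias is zero. Section 3.1.4 withdraws people for complications and worsening health, so if falls lead to withdrawal the effect could weaken or reverse.

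A reader might also infer a general inflation of the false-positive rate. For the proportion of fallers this depends on using the uncorrected chi-square test: Fisher's test stayed below 5% at 10%/30%. Finally, falls are one of several secondary outcomes, and the sample size rests on SPPB.

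**Conclusion.** The point holds as a conditional one. Unequal fall follow-up is built into 8.3, and no method in 10.2, as written, accounts for time at risk or is suited to a skewed count. If loss differs between arms, is unrelated to falls, and leavers stay in the denominator, the arm with more loss shows fewer falls at equal true rates. At an assumed 10%/30% split the reduction is about 11% (5% to 16% as *f* runs from 0.75 to 0.25). At 15%/25% with uniform exits it is about 5%, and at 20%/20% there is none. The loss splits, exit times, fall rates and dispersion are all assumptions. The primary SPPB result is unaffected. The change should be made because it is cheap and removes a dependence on dropout that the plan does not control, not because the documents show that bias will occur.

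**What to change.** In 10.2, add a paragraph on falls that does the following:

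- Defines the endpoint as falls per person-time, counted from the first class to the last day of diary follow-up.
- Specifies a negative binomial model with log link and log diary follow-up time as offset, with terms for arm and prior-year falls (already collected under 8.1). Poisson regression with robust standard errors is the fallback if the model does not converge.
- Includes all randomised participants with any follow-up after the first class, and reports by arm how many have none, since the offset is undefined for them.
- Reports the rate ratio with its 95% confidence interval, together with person-time and dropout by arm.
- Gives the proportion of fallers descriptively.

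The cost is mainly SAP wording, with one operational item. The documents do not say that the end of diary follow-up is recorded, so the last diary date must be captured for each participant. One limit remains: the offset does not correct for withdrawal that is itself related to falls. Reasons for withdrawal should therefore be shown beside the dropout figures.
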